### Pain

The global rating of pain is assessed by a single-item pain visual analog scale, which measures patient’s severity of pain over the previous week [43].

### Anxiety, depression

Anxious and depressive symptoms are measured with the nine-item Patient-Health-Questionnaire (PHQ-9), which is a validated tool for measuring DSM-IV depressive disorders [44]. The PHQ-9 is a shorter and more user-friendly form than other depression measurements and thus is being employed in the current study.

### Social support

The original questionnaire about social support (Fragebogen zur Sozialen Unterstützung, F-SozU) is a 54-item questionnaire from Germany covering a range of items about patients’ perception of emotional support, practical support, social integration, burden from the social network, reciprocity, availability of a confident, and satisfaction with social support; and has provided high reliability and validity [45]. We will employ the short F-SozU-14, as we anticipate that a reduction of items will contribute to patients’ compliance in answering the whole questionnaire pack, and reduce potential burden arising from high time exposure.

### Self-efficacy

Patients’ self-efficacy will be measured with the German version of the Self-Efficacy for Managing Chronic Disease 6-Item Scale (SES6G). This assessment tool has provided high internal consistency and good convergent construct validity [46]. Patients will be asked on 10-point Likert scales to indicate how confident they perceive themselves in handling their chronic illness.

### Patient competence

The concept of patient competence will be measured with the FEPK 2–57, which is a 57-item questionnaire involving five problem-focused and three emotion-focused subscales [34]. Patients will be asked on 5-point Likert scales how they perceive their competencies in coping with their disease with regard to employing self-managing strategies and communication with others. The questionnaire has provided satisfactory reliability; while external validity still needs to be evaluated and a short version composed.

### Spiritual wellbeing

Cancer patients’ quality of life [47] and CAM use [48] are associated with their spiritual well-being, which we will measure with the ‘Spiritual and Religious Attitudes in Dealing with Illness’ (SpREUK) instrument [49,50]. On 5-point Likert scales, participants are asked the extent to which they experienced aspects of search, faith, and reflection in the past week; thereby assessing how their confrontation with an existential illness resulted in their essential need to find meaningful answers and practices. We will employ the short form SpREUK-15 , which has provided high internal consistency and is considered to be suited for oncology populations [51].

### Patient satisfaction

For evaluating patients’ perceptions on the quality of medical and nursing care, we will employ the EORTC-QLQ-PATSAT32. This questionnaire has been validated in a cross-cultural context and provides excellent values for reliability and convergent validity [52].

### Quality of life (patients’ significant other)

The WHOQOL-BREF is a validated assessment tool for measuring generic quality of life in individuals [53]. We will employ this internationally widely employed tool to assess if patients’ HRQoL correlates with the QoL of their significant others (SOs). In addition, patients’ SOs will be asked to answer the German version of the Caregiver Quality of Life Index-Cancer (CQOLC), an instrument measuring specific and more accurate areas of the quality of life of significant others of patients with cancer [54]. The German translation is accessible in the Patient-Reported Outcome and Quality of Life Instruments Database (PROQOLID), but the psychometric properties of this version have not yet been reported [55].

### Accompanying research on economic data

Kligler and colleagues have shown that an integrative medicine approach including holistic nursing and a healing environment in an inpatient oncology setting can decrease anxiety, fatigue, and the use of medications resulting in substantial cost savings in the care of oncology patients [56]. Such evidence provides the rationale for including health economic analyses into our study plan. Secondary health economy-related endpoints will include the following:the cost of study treatments in intervention and control groups,the total cost of health care utilization and productivity losses in intervention and control groups during follow-up,the cost-effectiveness of trial intervention,the quality adjusted life years (QALY) gain or loss in intervention and control groups during follow-up, andthe cost per QALY in intervention and control groups.

The health economy analyses include the following steps:the assessment of the cost of the trial related intervention in the experimental groups and costs in the control groups,the collection of health service utilization data in the control and intervention groups during the follow-up,the assessment of longitudinal HRQoL data for transformation into preference measures and calculation of QALYs lost or gained during the follow-up, in order to calculate costs per QALY of interventions and controls, andthe calculation of the incremental cost-effectiveness ratio (ICER), cost-effectiveness acceptability curves (CEAC) and willingness-to-pay levels.

For collecting data on health services utilization during the follow-up, a scale [57] applied in international research will be adapted to the specific conditions of the German health care system and applied in the study sample (Mannheimer Module RV). To calculate QALYs, preferences generated from the EORCT-QLQ-C30 data will be used for patients [58], and WHOQOL-BREF data for patients’ SOs [53,59].

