**Primary outcome**								
Health-related quality of life	EORTC-QLQ-C30		X	X		X	X	X

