**Secondary outcomes**								
Nausea	MAT				X			
Fatigue	FACIT-F		X			X	X	X
Pain (general)	VAS		X			X	X	X
Anxiety, depression	PHQ-9		X			X	X	X
Social support	F-SozU K-14		X				X	X
Self-efficacy	SES6G		X			X	X	X
Patient competence	FEPK 2-57		X				X	X
Spiritual wellbeing	Sp-REUK-15		X				X	X
Patient satisfaction	EORTC-QLQ-PATSAT32						X	
Accompanying research (health economy)	Mannheimer Modul RV		X			X	X	
Quality of life SOs	WHOQOL-BREF		X				X	X
	CQOLC		X				X	X
**Others** Socio-demographic factors		X						
Cancer characteristics		X						
Medical history		X						
Treatment data			X		X	X	X	X

*EOI* end of intervention, *FU* follow-up, *PD* patient diary, *SOI* start of intervention, *SO* significant other.

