**Figure 2 Fig2:**
[figure not shown]
**Timeline.** EOI, end of intervention; FU, follow- up; IC, informed consent; ICI, initial counseling interview; SOI, start of intervention.

T0: Baseline assessment 1 to 2 weeks before the start of chemotherapy).T1: Start of intervention (SOI).T2: Mid-line (after the first half of the chemotherapy regimen; maximum of 12 weeks).T3: End of intervention (EOI) (after the end of the chemotherapy; maximum 24 weeks).T4: Follow-up, 6 months after the completion of chemotherapy (after maximum of 48 weeks).

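### Costs, QALYs and the ICER are promised over follow-up, but the cost instrument is not scheduled at the follow-up visit (T4)

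*Protocol article*

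**What the plan says.** The section Accompanying research on economic data sets the endpoints. The cost endpoint is "the total cost of health care utilization and productivity losses in intervention and control groups during follow-up". The effect side is "the assessment of longitudinal HRQoL data for transformation into preference measures and calculation of QALYs lost or gained during the follow-up". The two are then combined in a cost per QALY, an ICER, acceptability curves and willingness-to-pay levels.

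The same section names the instruments. The sentence that opens "For collecting data on health services utilization during the follow-up" assigns service use to the Mannheimer module, adapted to German conditions. Patient QALYs come from the QLQ-C30, and those of significant others from the WHOQOL-BREF.

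Table 1 sets the schedule. The row "Accompanying research (health economy)" carries "Mannheimer Modul RV" with marks at T1, T2 and T3 and none at T4. The row "Health-related quality of life" (QLQ-C30) is marked at T1, T2, T3 and T4 and weekly in the diary. The WHOQOL-BREF is marked at T1, T3 and T4.

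The Schedule section places T3 at the end of chemotherapy, at most 24 weeks. It describes T4 as "Follow-up, 6 months after the completion of chemotherapy (after maximum of 48 weeks)".

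**The concern.** The visit that the protocol calls follow-up is the one at which the cost instrument is missing, although that instrument is assigned to costs during follow-up. Both instruments that feed the QALYs are present there. Carried out as written, the schedule cannot deliver the stated cost endpoint for the months after chemotherapy. Service use and work absence in that window are part of what the endpoint is meant to capture.

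The gap also reaches the ratio. If the QALY calculation takes in the T4 data, costs and effects are measured over different periods, and the ICER and acceptability curves inherit the mismatch. An analysis plan can choose a horizon, but it cannot recover service use between T3 and T4 that nobody asked about.

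**Working it through.** The article gives no economic sample size, cost or ICER to reproduce. The check is a reading of Table 1 by column and the share of the horizon left without cost data.

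**Step 1: the schedule by column**

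| Instrument | Use in the economic analysis | T1 | T2 | T3 | T4 |
|---|---|---|---|---|---|
| Mannheimer Modul RV | service use | X | X | X | empty |
| QLQ-C30 | patient QALYs | X | X | X | X |
| WHOQOL-BREF | significant others' QALYs | X | empty | X | X |

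The empty cell is unlikely to be a table-reading fault. The Mannheimer row splits into nine cells, matching the nine column headers, and the last is blank. Other rows in the same table (FACIT-F, VAS, PHQ-9, SES6G) have the same marks at T1, T2 and T3 and do carry one at T4.

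**Step 2: other possible cost sources between T3 and T4**

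- Treatment data are marked at T4 in Table 1.
- The Control group section says that other supportive care is documented throughout the study.
- The diary has only weekly and per-cycle columns, and Table 1 assigns it no service-use or productivity instrument.

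The economic section uses none of these as a costing source. It also names no instrument for productivity losses. That the Mannheimer module supplies them is an inference from its being the only health-economy row.

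**Step 3: share of the horizon without scheduled cost data**

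Weeks are counted from the start of chemotherapy, and the uncovered share is (T4 − T3) / T4.

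| Case | T3 (weeks) | T4 (weeks) | Uncovered share |
|---|---|---|---|
| Stated maxima | 24 | 48 | 24/48 = 50% |
| 6 months read as 26 weeks | 24 | 24 + 26 = 50 | 26/50 = 52% |
| Assumed 18-week regimen | 18 | 18 + 26 = 44 | 26/44 = 59% |
| Assumed 12-week regimen | 12 | 12 + 26 = 38 | 26/38 = 68% |

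The last two regimen lengths are assumptions used to show the range.

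**Step 4: when this distorts the ICER**

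Write ΔC for the difference in mean cost between arms. Over the full period, ΔC(T1 to T4) = ΔC(T1 to T3) + ΔC(T3 to T4). The schedule supports only the first term. If the effect difference is taken to T4, the numerator is in error by ΔC(T3 to T4). That error is zero when the arms cost the same after chemotherapy. Otherwise it takes the sign and size of the difference, and the article gives no figure for either.

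**The case against.** The strongest reply is that the documents never say that QALYs run to T4. The same follow-up wording is used for costs and for QALYs, so the stated horizon is common to both. The QLQ-C30 is needed at T4 anyway, because it is the primary outcome instrument and the mixed model runs from T1 to T4. An analyst could stop both streams at T3, and a condensed article may leave the time window of the ICER to the full protocol. This stands as far as the ICER goes: the mismatch is conditional on T4 data entering the QALYs. It does not remove the contradiction between text and table. The article itself fixes both the endpoint and the schedule, labels T4 as the follow-up visit, and nowhere limits the QALYs to T3.

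A reader might also infer three stronger claims, which the documents do not support:

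- **Costs after chemotherapy will be counted as zero.** Nothing says how unobserved costs are handled.
- **The ratio is biased and cannot be interpreted.** Bias needs a cost difference between arms from T3 to T4, which is possible but not shown. The data to T3 would still support a ratio with a T3 horizon.
- **No cost-relevant data at all exist after T3.** Treatment data are marked at T4. The supportable statement is that no general service-use or productivity instrument is scheduled there.

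**Conclusion.** The inconsistency is real and should be corrected. The economic section promises costs during follow-up from an instrument that Table 1 does not schedule at the follow-up visit. At the stated maxima, 24 of 48 weeks (50%) have QALY instruments at their end but no general cost instrument; the share is 52% to 68% under the other timings considered.

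The consequence for the ICER and acceptability curves rests on two conditions: that the QALYs use T4 data, and that costs after chemotherapy differ by arm. Neither is stated in the article, so the direction and size of any distortion cannot be given. The primary HRQoL comparison is not touched.

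**What to change.** Reconcile the economic section with Table 1 on one horizon that applies to every patient. There are two ways.

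1. **Collect costs at T4.** Add the Mannheimer module, with service-use and productivity items, to the existing T4 pack, covering the time since T3, and mark it in Table 1. This costs one more questionnaire and a small patient burden. Recall would span about 6 months, whereas T1 to T2 and T2 to T3 are at most about 12 weeks each (24 − 12 = 12). The article gives no recall period for the adapted scale, so whether it suits the longer span needs checking.
2. **End the economic horizon at T3.** If T4 cost data cannot be obtained for all patients, for example because some have already passed T4, stop costs, QALYs, the ICER and the acceptability curves at T3 for everyone and state that horizon. This costs wording only, but gives up any economic conclusion about the months after chemotherapy.

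The two should not be mixed, with some patients costed to T4 and others to T3 in a single ICER. Under either option, name the source of the productivity losses.

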## Background

Gynecologic malignancies, including breast cancer, constitute approximately 95,600 new cases per year, which is nearly half (43%) of all malignancies in women in Germany [1]. It is known that health-related quality of life (HRQoL) is most negatively affected from the time of diagnosis through the completion of chemotherapy [2]. In this demanding phase, many patients are looking for help and orient themselves towards the field of complementary and alternative medicine (CAM). Consequently, the use of CAM by cancer patients has increased considerably over recent years [3], particularly in breast cancer populations [4].

Research suggests that cancer patients use CAM alongside their conventional therapy for a variety of reasons [5,6]. For example, patients use CAM to improve their HRQoL (for example, to relieve stress and anxiety and to alleviate side-effects of the chemotherapy) or they are motivated by the desire to maximize the success of treatment through their own actions (‘self-efficacy’) [3,7]. Overall, CAM use constitutes a form of coping strategy that helps cancer patients and their involved significant others (SOs), like family members and close friends, to overcome the distressing cancer diagnosis [8].

In a German sample of 1,030 patients with gynecologic and breast cancer, CAM was used by 49% of all women (50% in breast cancer patients versus 44% in gynecologic cancer patients). In this study, CAM users less frequently stated an overall deterioration of their health status (35%) compared to nonusers (50%) [9]. These numbers are in line with international studies where the rate of CAM use in women with breast cancer has been reported to be even higher (up to 75%), with the highest percentages in women undergoing chemotherapy [10].

Worldwide, oncologists have acknowledged that CAM may contribute positively to patients’ psychological and physical well-being and have started to develop guidelines on integrating CAM within a quality-controlled, evidence-based strategy [11-13] concluding that there is a lack of expert guidance available to patients. It has been suggested that oncology nurses are in a key position to evaluate which symptoms or side-effects patients are experiencing and to identify which CAM therapies may be helpful for symptom control related to treatment and psychological distress due to their cancer and the chemotherapy [14,15].

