The majority of breast and gynecologic cancer patients receive adjuvant or neoadjuvant chemotherapy, which may help to cure their cancer, or prolong life, but also affects their HRQoL due to treatment side-effects or psychosocial concerns [63]. Research consistently demonstrates that cancer patients have a high interest in complementing their conventional cancer treatment by using CAMs [3,5], and some integrative cancer centers have incorporated patients’ preference in providing counseling and methods reflecting a holistic treatment approach [18]. There is, however, a lack of research investigating the effects of such integrated services on a range of patient-centered outcomes in cancer patients treated with chemotherapy [64]. Previous randomized trials mostly investigated the efficacy of one CAM therapy on primary and secondary outcomes [65-68]. Likewise, other effectiveness studies, including nonpharmacologic interventions focused on investigating cognitive or educational programs, however, excluded CAM therapies [69,70] not knowing if patients applied CAM nevertheless. The current study aims to address this aspect by supplying patients in the control group with a patient diary to collect data related to physical and psychological symptoms as well as other supportive therapies patients may apply. While many intervention studies with cancer patients aimed to target cancer-related fatigue (CRF) [71-73], the CONGO study is designed to investigate if cancer patients’ and their significant others’ quality of life will be affected by the complex CAM nursing intervention.

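### One secondary economic endpoint, a separate cost per QALY for each arm, can be uninterpretable or misorder the arms; the planned incremental analysis should carry the conclusion alone

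*Protocol article*

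**What the plan says.** The protocol article introduces a list of five economic endpoints with "Secondary health economy-related endpoints will include the following". The fourth is "the quality adjusted life years (QALY) gain or loss in intervention and control groups during follow-up". The fifth is the "cost per QALY in intervention and control groups". The analysis steps in the same section link the two: longitudinal HRQoL data are turned into preference measures, followed by "calculation of QALYs lost or gained during the follow-up, in order to calculate costs per QALY of interventions and controls". Utilities come from the cancer questionnaire: "preferences generated from the EORCT-QLQ-C30 data will be used for patients".

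The list also has a separate endpoint for the cost-effectiveness of the intervention. The last analysis step plans an ICER, cost-effectiveness acceptability curves (CEAC) and willingness-to-pay levels. The per-arm ratio is therefore an additional quantity and not loose wording for the ICER.

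On the expected course, *Background* says that "health-related quality of life (HRQoL) is most negatively affected from the time of diagnosis through the completion of chemotherapy", and *Discussion* says that chemotherapy "also affects their HRQoL due to treatment side-effects or psychosocial concerns". Table 1 has the first QLQ-C30 at T1, the start of the intervention. The section gives no cost, utility or QALY figure, and it does not say whether its groups are the randomized arms only.

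**The concern.** A ratio of cost to QALYs informs a decision when numerator and denominator are both differences between the alternatives. The fifth endpoint instead divides each arm's cost by that arm's own QALYs, and the text allows two readings of the denominator.

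- **Change within the arm.** The words about loss and gain point this way. A change can be negative, zero or positive. Cost over a negative change has no value-for-money meaning, and near zero the ratio becomes arbitrarily large.
- **QALYs accumulated in the arm.** The ratio is then positive and stable. It is dominated by the costs and survival time that both arms share, so it hardly responds to what the intervention adds.

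At stake is a pair of published per-arm figures that could contradict the ICER printed beside them. The primary HRQoL comparison is not involved.

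**Working it through.** The article has no economic figure to reproduce. All utilities and costs below are assumptions, in arbitrary currency units. The visit weeks 0, 12, 24 and 48 are the maxima in the schedule under Figure 2. QALYs are the trapezoid area under utility, divided by 52.

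**1. Change within the arm**

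- Control: utilities 0.75, 0.60, 0.60, 0.75 and cost 10,000. Area = 8.1 + 7.2 + 16.2 = 31.5; 31.5/52 = 0.6058 QALYs.
- Intervention: half the drop (0.75, 0.675, 0.675, 0.75) and cost 10,500. Area = 8.55 + 8.1 + 17.1 = 33.75; 33.75/52 = 0.6490 QALYs.
- Constant T1 level: 0.75 × 48/52 = 0.6923 QALYs.
- Changes: 0.6058 - 0.6923 = -0.0865 and 0.6490 - 0.6923 = -0.0433.
- Per-arm ratios, from unrounded changes: 10,000/-0.0865 = -115,556 and 10,500/-0.0433 = -242,667.
- ICER: 500/0.0433 = 11,556 per QALY.

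**2. Does the order of negative ratios track value?** When both denominators are negative, raising an arm's cost lowers its signed ratio, and reducing its QALY loss raises the absolute size of its ratio. So reading by sign gets cost backwards, and reading by size gets benefit backwards.

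| Assumed case (control: cost 10,000) | Control ratio | Intervention ratio | What the ratios suggest |
|---|---|---|---|
| Equal loss -0.05; intervention costs 12,000 | -200,000 | -240,000 | By sign, the costlier arm looks better |
| Equal cost; loss -0.025 against -0.05 | -200,000 | -400,000 | Right by sign; by size, the better arm looks worse |
| Intervention 9,000 and -0.048 against -0.05 (dominant) | -200,000 | -187,500 | By sign, the dominant arm looks worse |
| Intervention 10,500 and +0.01 against -0.01 | -1,000,000 | 1,050,000 | By sign, control looks better; ICER is 500/0.02 = 25,000 |

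For frequency, 400,000 pairs of arms were drawn uniformly, with costs from 8,000 to 12,000 and QALY changes from -0.10 to -0.005. Where one arm dominated, the order was wrong in 13.5% of pairs by sign and 86.5% by size. Over all pairs, judged by net benefit at 50,000 and 20,000 per QALY, it was wrong in 29% and 43% by sign, and in 71% and 57% by size. With both arms gaining (0.005 to 0.10), no dominance case was misordered, but 15% and 29% of all pairs still were. These shares depend on the assumed ranges.

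**3. Is a net loss certain?** No. Utility changes from T1 of -0.10, -0.10 and 0 at T2, T3 and T4 give (-0.6 - 1.2 - 1.2)/52 = -0.058 QALYs. Changes of -0.05, 0 and +0.10 give (-0.3 - 0.3 + 1.2)/52 = +0.012. Both are small, so the sign is open and the denominator is near zero.

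**4. Accumulated QALYs**

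- Control as in step 1: 10,000/0.6058 = 16,508.
- Intervention with a small benefit (0.61 at T2 and T3, cost 10,500): (8.16 + 7.32 + 16.32)/52 = 0.6115 QALYs; 10,500/0.6115 = 17,170.
- The ratios differ by 4% (17,170/16,508 = 1.04). The ICER is 500/0.00577 = 86,667.

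For positive QALYs and a QALY gain, the intervention's average ratio is the lower one exactly when the ICER is below control's own average ratio. Comparing the averages thus applies a threshold set by the control arm. With utility 0.65 over 48 weeks (0.60 QALYs) and losses of 0.05 and 0.025, the ratios are 10,000/0.55 = 18,182 and 10,500/0.575 = 18,261, so control looks slightly better. The ICER is 500/0.025 = 20,000, and at 30,000 per QALY the net benefit of the intervention is 30,000 × 0.025 - 500 = +250.

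**The case against.** The strongest reply is that the decision quantity is already planned. The ICER, CEAC and willingness-to-pay levels are named, and nothing says that the per-arm ratios will rank the arms. This stands, and it limits the point to one secondary endpoint. A reader might infer that the trial's cost-effectiveness conclusion rests on the faulty ratio; the article does not support that.

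A reader might also infer that the protocol predicts a QALY loss in both arms. It does not. The adverse period it describes begins at diagnosis, so T1 already lies inside it, and T4 comes six months after chemotherapy. A net loss from T1 is plausible, but neither stated nor sized.

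Nor do negative ratios always misrank. In step 1, taking the lower signed value as better favours the intervention, which agrees with the ICER at any willingness to pay above 11,556. The supportable claim is that the order can be wrong.

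Finally, the article leaves the reference level for the QALY change undefined, a detail that a fuller economic plan may settle, and an average cost per QALY is a legitimate description. In the 4% example it even points the same way as the high ICER. Both remarks are fair, but neither denominator turns the per-arm ratio into a measure of what the intervention adds.

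**Conclusion.** The point holds for one of five secondary economic endpoints. On the change reading, the per-arm cost per QALY has no value-for-money meaning when the change is negative and is unstable near zero; its order can then contradict the incremental result. On the accumulated reading it is an average ratio that hardly reflects the increment (4% apart against an ICER of 86,667 in the example).

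The size in this trial cannot be known, because every cost and utility used here is assumed. What does not depend on those values is the direction of the fault: with negative denominators, reading by sign rewards cost and reading by size penalises benefit. The planned incremental analysis, the primary endpoint and the sample size are unaffected. The change is still worth making, because this is a stated analysis and not merely an omitted detail.

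**What to change.** Delete the per-arm cost per QALY from the endpoint list, together with the analysis step that produces it. Report mean cost and mean QALYs for each arm descriptively.

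Base the cost-effectiveness conclusion only on between-arm differences in the randomized patients, since *Design of the study* itself says that the preference arms suffer from selection bias. Adjust the QALY difference for T1 utility, which the T1 questionnaire already supplies and which parallels the baseline adjustment in the primary model. Present the result as the planned ICER and CEAC, and add incremental net benefit over the planned willingness-to-pay levels, which stays interpretable when both arms lose QALYs.

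The cost is a change of wording and one listed secondary ratio given up. No new data or patients are needed.
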